## Pharmacy Register Data Collection Form

### VERIFICATION AND FACILITY INFORMATION

|                                      |             |                  |                          |
|--------------------------------------|-------------|------------------|--------------------------|
| Data is complete and accurate | Name | Signature | Date (dd/mm/yyyy) |
| 2.1 Enumerator                |             |                  | / / 2014                 |
| 2.2 Supervisor                |             |                  | / / 2014                 |
| 2.3 Name of facility          |             |                  |                          |

ELIGIBILITY: ALL PATIENTS ON 1ST LINE TREATMENT, 18YEARS OLD OR OVER WHO MADE AT LEAST ONE APPOINTMENT DURING THE PREVIOUS 3 MONTHS

### PATIENT INFORMATION

| 2.4 Patient ID number | 2.5 Sex (M/F) | 2.6 Date of Birth (dd/mm/yyyy) | 2.8 Drug(s) dispensed | 2.9 Dose/ Frequency | 2.10 Quantity | 2.11 Next visit (dd/mm/yyyy) |
|-----------------------|---------------|--------------------------------|-----------------------|---------------------|---------------|------------------------------|
|                       | M F           |                                |                       |                     |               |                              |
|                       | M F           |                                |                       |                     |               |                              |
|                       | M F           |                                |                       |                     |               |                              |
|                       | M F           |                                |                       |                     |               |                              |

*NOTE: This data will be collected electronically where it is available.*

## ART stock-out form

### VERIFICATION AND FACILITY INFORMATION

|                                         |             |                  |                          |
|-----------------------------------------|-------------|------------------|--------------------------|
| Data is complete and accurate    | Name | Signature | Date (dd/mm/yyyy) |
| Enumerator                       |             |                  | __/__/2014               |
| Supervisor                       |             |                  | __/__/2014               |
| Name of facility                 |             |                  |                          |
| Name of storeroom contact        |             |                  |                          |
| Designation of storeroom contact |             |                  |                          |
| Storeroom contact phone number   |             |                  |                          |

*Please list dates of all stock-outs of first-round ARVs that occurred since September 1st, 2014*

| Commodity | Stock-out start date | Stock-out end date |
|-----------|----------------------|--------------------|
|           |                      |                    |
|           |                      |                    |
|           |                      |                    |
|           |                      |                    |
|           |                      |                    |
|           |                      |                    |
|           |                      |                    |
|           |                      |                    |
|           |                      |                    |
|           |                      |                    |
|           |                      |                    |
|           |                      |                    |
|           |                      |                    |
|           |                      |                    |
|           |                      |                    |

## Key Informant Interview

### 1 PRELIMINARY INFORMATION

|     |                |   |   |  |   |   |   |   |   |   |   |   |
|-----|----------------|---|---|--|---|---|---|---|---|---|---|---|
| 1.1 | Interview date |   |   |  | / |   |   | / |   |   |   |   |
|     |                | D | D |  |   | M | M |   | Y | Y | Y | Y |

|                         |  |
|-------------------------|--|
| NAME OF FACILITY |  |
| Name of facility        |  |

|                     |                                        |      |   |   |   |   |           |   |   |   |   |   |
|---------------------|----------------------------------------|------|---|---|---|---|-----------|---|---|---|---|---|
| VERIFICATION |                                        |      |   |   |   |   |           |   |   |   |   |   |
| 1.1                 | Start time                             |      |   | : |   |   | End time  |   |   | : |   |   |
|                     |                                        | H    | H |   | M | M |           | H | H |   | M | M |
|                     | Survey is complete and accurate | Name |   |   |   |   | Signature |   |   |   |   |   |
| 1.2                 | Enumerator                             |      |   |   |   |   |           |   |   |   |   |   |
| 1.3                 | Supervisor                             |      |   |   |   |   |           |   |   |   |   |   |

|                            |                                                                                                                            |     |  |   |                      |
|----------------------------|----------------------------------------------------------------------------------------------------------------------------|-----|--|---|----------------------|
| SCREENING QUESTIONS |                                                                                                                            |     |  |   |                      |
| 1.4                        | After reading the consent form.
Has the participant clearly read the consent form and provided informed consent? | No  |  | 1 | END           |
|                            |                                                                                                                            | Yes |  | 2 |                      |
| 1.5                        | After reading the consent form.
Has the participant agreed to have the conversation recorded?                    | No  |  | 1 | DO NOT RECORD |
|                            |                                                                                                                            | Yes |  | 2 |                      |

|     |                       |                 |  |    |
|-----|-----------------------|-----------------|--|----|
| 1.6 | Language of interview | English         |  | 1  |
|     |                       | Other, specify: |  | 98 |

## 2. PARTICIPANT INFORMATION

| DEMOGRAPHICS |                                                   |        |  |        |  |
|--------------|---------------------------------------------------|--------|--|--------|--|
| 2.1          | Age                                               |        |  |        |  |
| 2.2          | Sex                                               | Male   |  | 1      |  |
|              |                                                   | Female |  | 2      |  |
| 2.3          | How long have you worked at this facility/office? | Years  |  | Months |  |

## 3. BASELINE ASSESSMENT QUESTIONS FOR HEALTH FACILITY PARTICIPANTS

|     |                                                                                                                       |                                 |  |   |  |
|-----|-----------------------------------------------------------------------------------------------------------------------|---------------------------------|--|---|--|
| 3.1 | What is your cadre?                                                                                                   | Doctor or Medical
Licentiate |  | 1 |  |
|     |                                                                                                                       | Clinical Officer                |  | 2 |  |
|     |                                                                                                                       | Nurse                           |  | 3 |  |
|     |                                                                                                                       | Pharmacy staff                  |  | 4 |  |
|     |                                                                                                                       | Other, specify:
_____        |  | 5 |  |
| 3.2 | At this facility, who decides the number of refill months a patient gets?                                             |                                 |  |   |  |
| 3.3 | Does this facility have a policy about the number of ARV refill months patients should get?                           |                                 |  |   |  |
| 3.4 | IF YES, Describe policy.                                                                                       |                                 |  |   |  |
| 3.5 | IF NO, What most influences the decision around how many refill months to give a patient? (rank top 3 reasons) | 1.

2.

3.          |  |   |  |
| 3.6 | What do you think works well within this ART clinic?                                                                  |                                 |  |   |  |
| 3.7 | What are the main challenges you face in working in this clinic?                                                      |                                 |  |   |  |

|      |                                                                                                                                                                                                                     |  |
|------|---------------------------------------------------------------------------------------------------------------------------------------------------------------------------------------------------------------------|--|
| 3.8  | Do you think it would be a good thing to provide stable patients with 3-month prescriptions? Why or why not?                                                                                                        |  |
| 3.9  | What do you think are the main challenges or issues with providing patients with 3 month refills?                                                                                                                   |  |
| 3.10 | What kinds of changes would you suggest to improve the way this facility operates or how it provides care?
Prompt: Once finished initial response, ask specifically about congestion and 3 month refills. |  |

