### 4.1 *Objectives*

The primary objectives are:

1. Critically assess the failures and challenges related to clinic efficiency and supply chain and their role in preventing the provision of 3-month ART refills.
2. Plan and execute a set of interventions based on the assessment of failures and challenges related to facility congestion.
3. After implementation of the interventions, to determine their impact on the proportion of stable ART patients on 3-month refills.

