### *5.3 ART refill length*

One factor affecting facility congestion is the proportion of stable ART patients receiving 3-month refill prescriptions. With longer prescription refill length, as compared to the frequently dispensed 1- or 2-month prescriptions, stable patients are able to space out their facility visits, and thus, reduce the number of people within the facility at any given time. The Zambian ART Guidelines recommend that stable ART patients be provided with prescriptions for up to 3 months at a time, but few patients in Zambia receive such prescriptions.

To assess refill patterns within Zambian facilities, our team conducted assessments at five ART clinics in Lusaka. The majority of patients received their ART refill for one month or less (51%), 26% of patients received a 2-month refill and 23% received a 3-month refill. The decision on the ideal refill length is often decided by a team (including adherence counsellors and clinicians), however the pharmacist made the final decision based their knowledge of drug stock levels. The In-Charge of facilities reported that unreliable stocks of ARTs were the main barrier to the provision of 3-month refills for stable patients.

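### The only ranked question on what drives refill length is put only to staff who report no facility refill policy, so the ranking is lost for everyone who reports one

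*Combined protocol and SAP*

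**What the plan says.** Annex 6, section 3 is the baseline interview for health facility staff. Item 3.2 asks all of them "At this facility, who decides the number of refill months a patient gets". Item 3.3 then asks "Does this facility have a policy about the number of ARV refill months patients should get". The next two items are alternatives. For a yes, item 3.4 reads "IF YES, Describe policy". For a no, item 3.5 reads "IF NO, What most influences the decision around how many refill months to give a patient? (rank top 3 reasons". Items 3.6 to 3.10 carry no condition; among them, item 3.9 asks "What do you think are the main challenges or issues with providing patients with 3 month refills".

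The interview serves the first primary objective in section 4.1: "Critically assess the failures and challenges related to clinic efficiency and supply chain and their role in preventing the provision of 3-month ART refills". Section 6.3.2 says that the intervention will be designed from this assessment.

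Section 5.3 gives the background. It states: "The Zambian ART Guidelines recommend that stable ART patients be provided with prescriptions for up to 3 months at a time". It goes on to say that few patients receive prescriptions of that length, and that the pharmacist made the final decision from knowledge of stock.

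**The concern.** The routing treats a policy as an explanation of the refill length. That is reasonable only where the policy is followed. Where a policy exists and practice departs from it, the respondent describes the policy and is never asked to rank what sets the length in its place. Section 5.3 gives grounds to expect departures of this kind, at least from the national recommendation.

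At stake is information on relative importance. Objective 1 asks about the role of each failure in preventing longer refills, and the intervention has to be aimed at something. A ranked list from all facility respondents would help to choose. A list from only those who report no policy describes a subgroup defined by the answer to another question.

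**Working it through.** No arithmetic in the plan depends on this item, so the check is a trace of the form and a search for a substitute.

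**1. Trace of Annex 6, section 3.**
- Policy reported: 3.2, 3.3, 3.4, then 3.6 to 3.10. Item 3.5 is not asked.
- No policy reported: 3.2, 3.3, 3.5, then 3.6 to 3.10.

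On neither branch does an item ask whether a policy is followed, or why not.

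**2. Does another instrument supply the ranking?**
- Items 3.2, 3.7, 3.8, 3.9 and 3.10 are asked on both branches. They cover who decides, the clinic's main challenges, whether 3-month prescriptions are a good thing, barriers to them, and suggested changes with a prompt on 3-month refills. All are open text and none asks for a ranking.
- Section 6.3.1 plans data collection at the pharmacy to find the rationale for the refill interval. The pharmacy register form (Annex 4) has fields for drug, dose, quantity and next visit, but none for a reason.
- The stock-out form (Annex 5) records commodities and dates. It does not link a stock-out to a refill length and covers no other driver.
- The district pharmacist and Medical Stores Limited sections of Annex 6 ask about supply and about challenges with 3-month refills. They do not ask what sets the length at a given clinic.
- The endline staff section of Annex 6 does not repeat item 3.5.

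Barriers are therefore captured in several places; a ranking of drivers is captured only in item 3.5.

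**3. Can a policy stand in for practice?** In the five-clinic assessment in section 5.3, 51% of patients received one month or less and 26% received two months, so 51% + 26% = 77% received less than three months. These figures are for patients as reported there and are not restricted to stable patients, so they do not measure non-adherence to the recommendation. Together with the statement that few patients receive such prescriptions, they show that a recommendation and a different practice can exist side by side.

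**4. Size.** Let n be the number of facility staff interviewed at baseline and p the share who report a policy. Ranked answers available = n × (1 − p). The documents give no value for p, so the full range applies:
- p = 0: n × 1, nothing is lost.
- p = 0.5: n × 0.5, half of the rankings are lost.
- p = 1: n × 0, all are lost.

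**The case against.** The strongest reply is that the diagnosis does not rest on item 3.5. Item 3.9 asks every facility respondent about obstacles to 3-month refills, which is close to the wording of objective 1, and items 3.2, 3.7, 3.8 and 3.10 add to it. Section 6.3.1 also lists supply-chain reports, patient flow, exit interviews and a review of procedures, and district and central supply staff are interviewed without any policy condition. In the preliminary assessment, facility heads had already named unreliable stock as the main barrier. This stands: staff at a clinic with a policy can still say that stock, or anything else, prevents longer refills.

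A reader might go further than the documents allow in three ways.
- *That staff who know the national guideline will answer yes to item 3.3.* The item asks about a policy of the facility, whereas section 5.3 describes a national recommendation. Equating the two is plausible but not documented.
- *That a number of facilities, or of matched pairs, will lack rankings.* The condition works on each respondent. Section 6.1.2 plans interviews with clinicians of several cadres, and colleagues at one clinic may answer item 3.3 differently. Multiplying the 16 facilities by an assumed share does not follow from the form.
- *That a planned comparison between clinics or pairs is damaged.* Sections 6.5 and 6.5.1 plan no comparison of ranked reasons. They plan a qualitative description of process, and the informants are chosen purposively.

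What survives the reply is narrower: open text shows which barriers are mentioned, but not which one a respondent puts first as the driver of the length actually given.

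**Conclusion.** The point holds as a minor weakness of the baseline assessment. The ranked measure of drivers is missing by design for every respondent who reports a facility policy, no item asks whether that policy is followed, and no other form supplies the ranking. The loss falls somewhere between none and all of the rankings.

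A reader might infer that the trial cannot find out why refills are short. The documents do not support that, because objective 1 covers efficiency and supply failures broadly and the unconditional questions reach them. The conclusion rests on reading the printed conditions literally, as an interviewer would. It has no bearing on the primary outcome, the sample size or the primary analysis.

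**What to change.** Delete the condition at the start of item 3.5 and put the item to every facility respondent after 3.3 and, where it applies, 3.4. Reword it so that it asks about practice: *In practice, what most influences how many refill months a patient is given? (Rank top 3.)* Item 3.4 can stay as it is, so that a described policy and the stated drivers can be read side by side for the same respondent.

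The cost is one changed instruction and about one extra minute per interview. The change should be made before the baseline interviews, since the endline section does not ask the question again.

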#### 4. ENDLINE ASSESSMENT QUESTIONS FOR HEALTH FACILITY PARTICIPANTS

|     |                                                                                                                                                                                                                 |                              |  |   |  |
|-----|-----------------------------------------------------------------------------------------------------------------------------------------------------------------------------------------------------------------|------------------------------|--|---|--|
| 4.1 | What is your cadre?                                                                                                                                                                                             | Doctor or Medical Licentiate |  | 1 |  |
|     |                                                                                                                                                                                                                 | Clinical Officer             |  | 2 |  |
|     |                                                                                                                                                                                                                 | Nurse                        |  | 3 |  |
|     |                                                                                                                                                                                                                 | Pharmacy staff               |  | 4 |  |
|     |                                                                                                                                                                                                                 | Other, specify:
_____     |  | 5 |  |
| 4.2 | Are you aware that a program is being implemented at this facility to increase the proportion of stable patients on 3-month ART refills?                                                                        |                              |  |   |  |
| 4.3 | Please describe any changes that have taken place in the last 4 months in the way this facility provides services to ART patients?                                                                              |                              |  |   |  |
| 4.4 | What are the main challenges that you have experienced as these changes have been implemented?
Your feedback is important to improving care at this facility, so please feel free to answer honestly. |                              |  |   |  |
| 4.5 | Have the recent changes had a positive impact on your experience and/or on the care that patients get?                                                                                                          |                              |  |   |  |

#### 5. QUESTIONS DISTRICT PHARMACISTS

|     |                                                                                                                                   |  |
|-----|-----------------------------------------------------------------------------------------------------------------------------------|--|
| 5.1 | What is your position and department?                                                                                             |  |
| 5.2 | What do you see as the main challenges in providing health facilities with the ART supplies that they request in a timely manner? |  |
| 5.3 | What parts or aspects of the ART supply chain that work well?                                                                     |  |
| 5.4 | What do you think is a way to improve the supply system for ART drugs?                                                            |  |
| 5.6 | What portion of stable ART patients in Lusaka do you think are getting 3-month prescriptions now?                                 |  |
| 5.6 | Do you think it is a good thing to provide most stable patients with multi-month prescriptions? Why or why not?                   |  |
| 5.8 | What do you think are the main challenges or issues with providing patients with 3-month refills?                                 |  |
| 5.9 | What kinds of changes do you think would be needed to provide more patients with 3 month refills?                                 |  |

